#### Evaluation of Gut Microbiome–Related Metabolites and Gut Microbiome Change

Blood samples will be used to assess changes in gut microbiome–related metabolites. Blood will be collected from participants after an 8-hour fast before blood collection, and changes in metabolites will be determined using liquid chromatography-mass spectrometry and gas chromatography-mass spectrometry analyses. Western blotting will be applied to confirm changes in strain-derived factors in the blood of patients with PD. Participants’ fecal samples will be used to analyze the composition of the gut microbiome using 16S rRNA sequencing and fecal microbiome transplantation to assess the correlation between gut microbiome and response to acupuncture treatment. A small amount of feces will be collected using 4N6 FLOQSwabs (Copan Diagnostics Inc). For participants with PD, 2-3 g of feces will be collected using a Stool Collection Tubes With DNA Stabilizer (Invitek Diagnostics) for fecal microbiome transplantation. A FastDNA SPIN Kit for Feces (MP Biomedicals) will be used to isolate DNA from feces for DNA extraction and sequencing. DNA will be subjected to polymerase chain reaction targeting the V3-V4 variable region of bacterial 16S rRNA as a template, followed by sequencing library construction and sequencing reactions on the MiSeq Platform (Illumina, Inc). Sampling will be conducted at day 0, 6 weeks, 12 weeks, and 20 weeks in participants with PD and after screening in healthy participants.

#### Evaluation of Digestive Symptoms

Abdominal examination is a Korean medicine diagnostic method based on the Korean medicine theory that when a disease is inside the body, its response manifests on the body surface [32]. Participants will undergo manual palpation of Zhongwan (CV12) and Tianshu (ST25) for tenderness, while the presence or absence of gastric stuffiness and rigidity below the heart will be checked. The GSRS is a globally used self-reported gastrointestinal symptom scale that covers upper and lower gastrointestinal symptoms [33]. It comprises 15 questions in 5 domains (abdominal pain, reflux syndrome, indigestion syndrome, diarrhea syndrome, and constipation syndrome) scored on a 7-point scale from 1 (no symptoms) to 7 (very severe symptoms). The TDS has been used in previous studies to assess functional dyspepsia [34,35] and comprises 8 items (postprandial fullness and bloating, early satiety, epigastric pain, epigastric burning, nausea, vomiting, belching, and other symptoms) rated on a scale of 0 (absent) to 3 (severe). The BSS is the most widely used measure of stool formation, ranging from the hardest (type 1) to the softest (type 7) [36]. Evaluation will be conducted at day 0, 6 weeks, 12 weeks, and 20 weeks in participants with PD and after screening in healthy participants.

#### Other Evaluations

The MYMOP is a 4-item self-reported health assessment tool that measures subjective symptom change in response to treatment [37]. Using a scale of 0 (as good as it could be) to 6 (as bad as it could be), participants rate the 1 or 2 symptoms that have worried them the most, important activities, and general well-being in the past week. It will be conducted at day 0, 6 weeks, 12 weeks, and 20 weeks in participants with PD and after screening in healthy participants. The credibility assessment in acupuncture trials assesses the patient's credibility of acupuncture treatment, rating 4 items on a scale of 1 (absolutely not) to 6 (absolutely yes) [38]. This tool will be used to evaluate the impact of psychological factors on the outcomes of patients' credibility of acupuncture and moxibustion treatment in this study. This assessment will be conducted at day 0, 6 weeks, and 12 weeks in participants with PD and after screening in healthy participants.

### Safety Assessments and Monitoring

At each visit, the participants’ subjective and objective adverse events will be investigated and classified into mild, moderate, and severe as follows: mild, participant feels little to no discomfort and symptoms interfere little with usual activities of daily living (ADL), most likely not requiring treatment; moderate, participant may experience discomfort that interferes with usual ADL, which may allow the participant to continue the study but may require treatment; severe, participant feels very uncomfortable, interfering with usual ADL, unable to continue participating in the study, and may require treatment or hospitalization. The causal relationship between reported adverse events, acupuncture treatments, and blood collection will be categorized by the Korean medicine doctor in charge as follows: more than 90%, definitely; 70%-90%, probably; 50%-70%, possibly; 30%-50%, probably not; and less than 10%, definitely not.

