### Safety Analysis

For all adverse events that occurred during treatment, the frequency of adverse events will be analyzed according to whether they were associated with treatment or not. The number and proportion of participants with at least one adverse event, 95% CI, and the number of occurrences will be presented.

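### The adverse-event causality bands leave 10% to under 30% without a category and overlap at 50% and 70%, and the safety analysis window is narrower than the events that are rated (minor)

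*Protocol article*

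**What the plan says.** Safety Assessments and Monitoring has adverse events asked about at each visit. The Korean medicine doctor in charge rates their causal relation to the acupuncture treatments and to blood collection, on a scale given in full: "more than 90%, definitely; 70%-90%, probably; 50%-70%, possibly; 30%-50%, probably not; and less than 10%, definitely not".

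Safety Analysis uses that judgement in a two-way split: "the frequency of adverse events will be analyzed according to whether they were associated with treatment or not". The events that enter are described as "For all adverse events that occurred during treatment". The same section also reports how many participants, and what proportion, had at least one adverse event, with a 95% CI and the number of occurrences. That summary does not use causality.

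Three other places bear on the point:

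- Interventions sets the treatment period at 12 weeks.
- The section on evaluating metabolites and the gut microbiome schedules sampling in patients at day 0 and weeks 6, 12 and 20, and in healthy participants after screening. Table 1 also lists a blood sample for healthy participants.
- The Discussion concedes that the treating doctors assess adverse events with no independent adjudication and no standardized grading. It does not mention a gap or an overlap in the causality scale.

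**The concern.** A rating scale that feeds an analysis should give every possible rating one category and only one. This scale fails on both counts. Below 30% the next band starts under 10%, so a rater who thinks an event 20% likely to be due to treatment has no box to tick. Two adjacent pairs of bands share an end point, and at 50% the choice is between a positive label and a negative one.

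An article may leave detail to the full protocol or the SAP, but that does not cover this case. The article sets out the complete scale, and the scale is wrong as printed.

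The second part concerns which events are counted. If causality is rated for blood collection, and blood is drawn after treatment has ended and in people who are never treated, then a safety analysis confined to the treatment period leaves out some of the events that the study rates.

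At stake are a clear rule for a limited set of ratings and a complete safety table. The efficacy and microbiome analyses are not affected.

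**Working it through.** **Coverage of the scale.** The inputs are the five bands in Safety Assessments and Monitoring. Printed range ends are read as included, and p is the rated percentage.

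| Band as printed | Condition | Whole percentages |
|---|---|---|
| "more than 90%, definitely" | p > 90 | 91-100 |
| "70%-90%, probably" | 70 ≤ p ≤ 90 | 70-90 |
| "50%-70%, possibly" | 50 ≤ p ≤ 70 | 50-70 |
| "30%-50%, probably not" | 30 ≤ p ≤ 50 | 30-50 |
| "less than 10%, definitely not" | p < 10 | 0-9 |

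Each whole percentage from 0 to 100 (101 values) is assigned to the bands whose condition it meets.

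- No band: 10 to 29, which is 20 values. On a continuous scale this is 10 ≤ p < 30, and (30 − 10)/100 = one fifth of the range.
- Two bands: 50 ('possibly' and 'probably not') and 70 ('probably' and 'possibly'), which is 2 values.
- One band: 0-9 (10 values), 30-49 (20), 51-69 (19), 71-90 (20) and 91-100 (10). The sum is 10 + 20 + 19 + 20 + 10 = 79.
- Check: 20 + 2 + 79 = 101.

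There is no overlap at 90%, because the top band starts above it.

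**Effect on the two-way split.** The article does not say which labels count as associated with treatment, so each possible cut is tried. A value is undecided if its possible labels fall on both sides of the cut. A value in the gap is taken to go to either neighbouring band, 'probably not' or 'definitely not'.

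| Labels counted as associated | Undecided ratings |
|---|---|
| definitely | none |
| definitely, probably | 70 only |
| definitely, probably, possibly | 50 only |
| all except definitely not | 10 to 29 |

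The gap lies between the two negative labels. It therefore changes the split only under the last cut.

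**Window.** Setting the sections side by side:

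- Treatment ends at week 12. The last blood sample in patients is at week 20, which is 20 − 12 = 8 weeks later.
- Healthy participants give a blood sample and receive no treatment.
- Causality is rated for blood collection as well as for acupuncture.
- The analysis covers events during treatment.

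Read literally, an event caused by the week-20 draw, or by any draw in a healthy participant, is rated but not analysed.

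**The case against.** The strongest reply is that the gap does no harm on the plain reading of the labels. 'Probably not' and 'definitely not' both mean unrelated, so wherever the doctor places a 20% rating, the related count stays the same. This stands, and it is why the effect is probably small. It does not repair the scale: the five-way classification is still undefined in that range, and the 50% overlap does cross from a positive to a negative label.

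A reader might infer that adverse events in general cannot be classified, or that the treatment-related rate cannot be reproduced. The documents do not support that, since 79 of 101 whole percentages have one category and most cuts leave at most one value undecided. A reader might also take 1/60 = 1.7 percentage points per reclassified patient as the size of the problem. Safety Analysis splits the frequency of events by association, and its participant proportion is for any adverse event. A related-event proportion of patients is not defined there, so the figure has nothing to attach to.

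The choice of labels that count as associated may well be in the full protocol or SAP, and its absence from an article is not a fault. Shared range ends are common shorthand, and the gap may be a slip made in condensing the protocol. Both are fair and bear on severity, but the printed text still needs correcting. The Discussion already discloses the unblinded treating assessor, so that is not a new criticism.

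On the window, the visit schedule for patients is in an appendix that is not shown, and the phrase about events during treatment may be loose wording. It is therefore not established that post-treatment events will be dropped. What the article shows is that its safety analysis, taken literally, does not cover all the blood draws whose events it rates.

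**Conclusion.** The point holds as a minor defect in two parts.

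First, the causality scale is incomplete from 10% to under 30% and ambiguous at 50% and 70%, so some events have no category or have two. The related/unrelated split is affected only at exactly 50% or exactly 70%, depending on the cut, unless 'probably not' counts as associated; then all ratings of 10-29% are undecided. The proportion of participants with at least one adverse event does not depend on the scale.

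Second, the analysis window is narrower than the set of rated events. It omits the week-20 draw and healthy participants' draws if read literally.

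This rests on reading the printed range ends as included, on the published scale being the one in use, and on 'each visit' including the week-20 visit. How many events fall in the gap, on a boundary or outside the window cannot be known from the article, so no numerical effect on the safety results can be given.

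**What to change.** 1. Make the bands contiguous and non-overlapping: close the gap between 10% and 30%, and use ≥ and < at 50 and 70. If the full protocol already has correct bands, correct the article instead.
2. When the bands are corrected, say which labels count as associated with treatment, or point to where the full protocol or SAP says so.
3. Observation has ended and analysis is under way, so the remedy depends on what was recorded. If numeric ratings were stored, resolve those in the gap or on a boundary by a written rule before tabulation. If only labels were stored, affected events cannot be identified; report the five labels as recorded and disclose the gap.
4. Tabulate all adverse events from first treatment or blood draw, whichever comes first, through the last visit. Include healthy participants' blood-draw events, and show on-treatment and post-treatment events separately.

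The cost is a wording change, possibly a short review of recorded ratings, and slightly more tabulation. The reported event count may rise slightly because of the wider window.

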### Sample Size

This study is not intended to statistically validate the intervention effect of acupuncture and moxibustion on PD but was rather conducted as an exploratory study comparing gut microbiome markers in patients with PD and healthy participants and the effects of acupuncture and moxibustion on the gut microbiome in patients with PD. Therefore, the sample size required for the study will be 60 patients with PD and 20 healthy individuals, depending on the financial resources and study environment, and in consultation with experts in gut microbiology.

### Statistical Analysis

#### Overview of Statistical Analysis

SPSS (ver 21.0, IBM SPSS Statistics for Windows) will be used for analysis. All measures will be presented as mean (SD) for continuous variables and as n (%) for dichotomous variables. For efficacy endpoints, the amount of change or rate of change from baseline to end of treatment and follow-up will be calculated.

All data obtained from participants will be analyzed in 2 forms: intention-to-treat (ITT) analysis and per-protocol (PP) analysis. The ITT analysis will be performed on all participants who undergo acupuncture and moxibustion at least once. For missing data on the evaluation variables, the last observation carried forward (LOCF) method will be applied. PP analysis will further be performed on participants who completed the entire study. The evaluation will be based on the results of the ITT analysis and is presented with reference to the PP analysis.

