## Methods

### Study Design

This protocol describes a single-group, prospective, observational study aiming to analyze differences in gut microbiome between patients with idiopathic PD and healthy participants, to observe changes in gut microbiome after 12 weeks of acupuncture and moxibustion in patients with PD, and to correlate these changes with changes in motor and nonmotor symptoms of PD that were altered by acupuncture and moxibustion treatment. The gut microbiome patterns at baseline in healthy participants and screened patients with PD will be analyzed to determine whether the gut microbiome of patients with PD is different from that of healthy participants. Patients with PD will be treated with acupuncture, moxibustion, and intradermal acupuncture twice a week for 12 weeks, yielding a total of 24 sessions. The motor and nonmotor symptoms of PD and gut microbiome changes in response to acupuncture and moxibustion will be compared before starting treatment (day 0), during treatment (6 weeks), at the end of treatment (12 weeks), and 2 months after the end of treatment (20 weeks). The correlation between motor and nonmotor symptoms of PD changed by acupuncture and moxibustion treatment and changes in gut microbiome will be analyzed. The enrollment, interventions, and assessments of patients with PD are summarized in Table S1 in Multimedia Appendix 1. A schematic of the study process is shown in Figure 1. Healthy participants will be assessed for motor and nonmotor symptoms of PD and gut microbiome after screening. The enrollment and assessment of healthy participants are summarized in Table 1. Kyung Hee University Korean Medicine Hospital, Seoul, Republic of Korea, will serve as the study site. The study protocol was registered with the Clinical Research Information Service (KCT0006669) on October 15, 2021. This protocol was reported in accordance with the SPIRIT (Standard Protocol Items: Recommendations for Interventional Trials) guidelines (Multimedia Appendix 2).

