#### Analysis for Changes in Clinical Outcomes

For the following clinical outcomes with continuous variables, the mean (SD), median, minimum, maximum, and maximum of each outcome will be presented for change in score from day 0 to 6 weeks, 12 weeks, and 20 weeks, and a 1-way repeated measures ANOVA will be performed to test for statistically significant changes in any of the following factors: total MDS-UPDRS score, total MDS-UPDRS score part I score, total MDS-UPDRS part II score, total MDS-UPDRS part III score, total MDS-UPDRS part IV score, BBS, TUG, S&E, PDQ-39, levodopa dosage investigation, abdominal examination, GSRS, TDS, BSS, and MYMOP.

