#### Changes in Gut Microbiome–Related Metabolites and Gut Microbiome

Differences in microbiome at each time point will be measured using weighted-unweighted UniFrac distance metrics and subsequently tested using analysis of similarity (ANOSIM). Correlations of clinical outcomes and treatment effects with key microbiomes will be analyzed using Spearman rank correlation analysis, with *P*<.05 considered significant. Principal component analysis will be applied to analyze metabolite distribution in the sample. Partial least squares-discriminant analysis will be applied to identify differences between patients with PD and healthy participants when analyzing metabolite distributions. Selected gut microbiome and metabolite changes will be analyzed by 1-way repeated measures ANOVA, with significant differences between time points determined at *P*<.05. The pathway analysis or enrichment analysis will be performed to analyze the metabolic pathways of the selected metabolites. The Kyoto Encyclopedia of Genes and Genomes database [39] will be used to identify interactions between metabolites. Receiver operating characteristic analysis will be conducted to confirm whether the selected metabolites reflect the representativeness of the disease or treatment.

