In the TEAM theory, the functional connection and communication between acupoints, the brain (ancient heart), and the gut is clinically important [54]. Based on the traditional theory, a previous review study [55] has reported that acupuncture has an effect on various diseases, including metabolic diseases, gastrointestinal diseases, mental disorders, and nervous system diseases, by regulating gut microbiome. Further, a large number of experimental studies on the relationship between PD and gut microbiome have been published recently, and the number is rapidly increasing [55]. In a previous experimental study including a PD model [19], we found that acupuncture treatment with GB34, which has been shown to exert neuroprotective effects on the brain, and ST36, which has been shown to enhance digestive function, improved motor function and anxiety, and increased the levels of dopaminergic fibers and neurons in the striatum and substantia nigra, increased the diversity of gut microbiome (alpha-diversity) and restored a gut microbiome to a composition more similar to that of robust controls (beta-diversity) compared with that noted in the PD group, in addition to restoring the increased levels of proteobacteria at the phylum level, suggesting that acupuncture exerts effects on improving gut microbiome imbalances. In another previous study [56], we conducted a clinical study to investigate whether acupuncture treatment for 2 weeks could effectively improve motor symptoms of PD using the UPDRS II+III in 73 patients with PD. This study showed that both the acupuncture treatment group and the control group showed improvement in motor function, with no significant intergroup difference; however, at the follow-up of 2 months after the end of treatment, the acupuncture treatment group continued to maintain these improvements in symptoms, while the control group reported a regression. Considering the results of these previous experimental studies, we hypothesized that acupuncture in this clinical study affected changes in gut microbiome to improve PD symptoms in a sustainable manner. To verify this hypothesis, we present the protocol of this study to explore changes in gut microbiome caused by acupuncture and moxibustion in patients with PD and explore its association with improvement in clinical symptoms of PD.

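### LOCF in the lead ITT analysis biases the week-20 result toward sustained improvement if benefit wanes, or dropouts worsen, after an initial gain

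*Protocol article*

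**What the plan says.** The protocol article fixes the handling of missing outcomes under Overview of Statistical Analysis: "For missing data on the evaluation variables, the last observation carried forward (LOCF) method will be applied". It defines two analysis sets: "The ITT analysis will be performed on all participants who undergo acupuncture and moxibustion at least once", and "PP analysis will further be performed on participants who completed the entire study". It also ranks them: "The evaluation will be based on the results of the ITT analysis and is presented with reference to the PP analysis".

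For the clinical outcomes, including the primary MDS-UPDRS, "a 1-way repeated measures ANOVA will be performed to test for statistically significant changes". The visits are day 0 and weeks 6, 12 and 20, the last being "2 months after the end of treatment (20 weeks"). The Discussion states what the authors expect: "we hypothesized that acupuncture in this clinical study affected changes in gut microbiome to improve PD symptoms in a sustainable manner".

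The dropout criteria (Textbox 3) cover, among others, patients who acquire a new infection or illness with a possible bearing on PD symptoms. The limitations in the Discussion mention neither LOCF nor missing data. No dropout rate, SD or expected effect is given, and the sample size of 60 patients with PD rests on feasibility.

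**The concern.** Week 20 is the only visit that can show whether a gain outlasts treatment. For a patient seen at week 12 but not at week 20, LOCF enters the full end-of-treatment change as the week-20 result. For a patient who left earlier, weeks 12 and 20 receive the same carried value. Either way the recorded week 12-to-20 change is exactly zero, so the imputation rule assumes maintenance, which is what the study hopes to show.

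A second route runs through the dropout criteria. A patient removed because of a new condition that may affect PD symptoms keeps the score recorded before that condition arose.

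The study has no untreated PD group, so the bias cannot partly cancel between arms. Loss of benefit after treatment is also not far-fetched. In the earlier acupuncture trial described in the Discussion both groups improved, and the control group had slipped back at two months, although the acupuncture group had not.

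**Working it through.** The plan has no figure of its own to reproduce. From the documents come the 60 patients, the four visits and the LOCF rule. A 5% level is stated for the microbiome and metabolite comparisons ("with significant differences between time points determined at" P<.05); it is taken here as two-sided, which the article does not specify. Everything else is assumed: scores in SD units (SD 1), correlation 0.7 between visits, mean change −0.3 at week 6 and −0.5 at week 12 (negative is better), dropout of 10–30%, and no return after dropout.

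**Week 12 to week 20.** With a share d missing at week 20 and dropout unrelated to outcome, LOCF change = (1 − d) × true change, whenever the patients left. A true loss of 0.50 SD is shown as 0.9 × 0.50 = 0.45, 0.8 × 0.50 = 0.40 and 0.7 × 0.50 = 0.35 at 10%, 20% and 30% missing.

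**Day 0 to week 20.** Bias = sum over dropout patterns of share × (mean at last observed visit − true week-20 mean). Suppose the benefit is fully lost, so the true change is 0.
- All dropout after week 12: bias = d × (−0.5).
- Dropout split equally over the three intervals: bias = (d/3) × (0 − 0.3 − 0.5) = −0.267d.

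A simulation of 6000 trials per scenario applied a paired t test to the day 0-to-20 change and counted significant results in the direction of improvement. Full data gave about 2.5%.

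| Dropout | Bias, all after week 12 | False improvement | Bias, evenly spread | False improvement |
|---|---|---|---|---|
| 10% | −0.05 | 7.0% | −0.027 | 4.9% |
| 20% | −0.10 | 15.4% | −0.053 | 7.5% |
| 30% | −0.15 | 29.1% | −0.080 | 13.0% |

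A run on other assumed inputs (SD 10, correlation 0.6, a 6-point gain fully lost, all dropout after week 12) gave spurious gains of 6 × d = 0.6, 1.2 and 1.8 points and false-improvement rates of 7%, 15% and 30%.

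**Dropouts who worsen.** Take half the benefit kept (−0.25), 20% lost after week 12, and those patients 0.5 SD worse at week 20.
- True mean: −0.25 + 0.2 × 0.5 = −0.15.
- LOCF: 0.8 × (−0.25) + 0.2 × (−0.5) = −0.30, twice the truth. Significant improvement appears in 83.3% of trials, against 29.5% with full data.
- Completers only: −0.25, so the PP set is also too favourable, by 0.10 SD.

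**Cases with no bias or the opposite bias.**
- Benefit fully kept, late dropout, no worsening: no bias.
- Benefit fully kept, 20% lost before week 6: LOCF shows 0.8 × (−0.5) = −0.40 against a true −0.50, which is conservative.
- Benefit fully lost, 20% lost before week 6: no bias (2.4% false improvement).
- Half the benefit kept, dropout evenly spread: bias = (d/3) × (0.25 − 0.05 − 0.25) = −0.017d, which is negligible.

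Early dropout is harmless only if those patients end no worse than their baseline. With half the benefit kept, 20% lost before week 6 and a 0.5 SD worsening, LOCF shows −0.20 against a true −0.15.

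**The case against.** A reader might infer that LOCF will manufacture a sustained improvement. The documents do not support that. LOCF cannot create a gain that was absent at the last observed visit, the cases above include nil and conservative bias, and the number, timing and reasons of dropouts are not given.

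The error rates need the same care. They belong to a day 0-to-20 contrast, not to the planned repeated measures ANOVA across all visits. In these scenarios there is a real gain at week 12, so a significant overall ANOVA would be a correct rejection. The upper rates also need a benefit that vanishes completely and dropout confined to the last interval.

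The planned PP analysis offers some protection. If dropout is unrelated to outcome, completers give an unbiased answer, and a gap between ITT and PP would be visible. That protection fails when dropout is related to outcome, which the dropout criteria make possible. They do not make it certain: they speak of conditions that may affect symptoms, not conditions known to worsen them.

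Other extensions are weak. The article applies LOCF to evaluation variables and does not say that microbiome profiles are carried forward. Unequal visit spacing does not in itself breach an ANOVA assumption.

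Finally, the study calls itself exploratory and admits that single-group changes may reflect progression or placebo. That lowers the stakes. It does not excuse a directional bias in the result that leads the report, and those caveats do not warn the reader about missing data.

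**Conclusion.** The point stands as a conditional bias. LOCF in the lead analysis records no change after the last observed visit, so it shrinks any true week 12-to-20 loss of benefit by the share missing, provided dropout is unrelated to outcome. It overstates the day 0-to-20 improvement when benefit wanes or dropouts worsen and patients leave after some gain. It is nil or conservative when patients leave before week 6 and end no worse than baseline, or when benefit is kept and dropouts do not worsen.

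Under the assumed inputs, with 60 patients and the benefit fully lost, false day 0-to-20 improvement rises from 2.5% to about 5–13% with evenly spread dropout of 10–30%, and to about 7–30% if all dropout follows week 12. The PP analysis escapes this bias only if dropout is unrelated to outcome.

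**What to change.** Lead with a mixed model for repeated measures on all observed values: visit as a categorical factor, unstructured within-patient covariance, no imputation. Report the day 0-to-12, day 0-to-20 and week 12-to-20 contrasts with 95% CIs. Tabulate dropout by visit and reason. Keep LOCF, if at all, as a labelled sensitivity analysis.

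Add a sensitivity analysis for data missing not at random. The mixed model assumes missing at random and was not fitted in this check. In the worsening-dropout example nothing observed predicts the decline, so the model would be expected to give about −0.25 against a true −0.15: better than −0.30 under LOCF, but not right.

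No new data are needed, and the named software has a mixed-model procedure. The costs are reliance on missing at random, CIs that may be slightly wider, and a change made after observation ended. The Results section says analysis is under way, so the change and its date should be disclosed.
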